### Participant withdrawal criteria

Participants who meet the criteria summarized in Table 3 will be discontinued from the trial. The subjects who are withdrawn after randomization will be followed up for outcomes. Reasons for withdrawal will be documented in case report forms (CRF) and data will be analyzed using the intention-to-treat (ITT) principle. Each site research coordinator will be responsible for making next-visit reminder phone calls to prevent a participant’s withdrawal.

**Table 3 Tab3:** Participant withdrawal criteria of the *Sipjeondaebo-tang* study

Participant withdrawal criterion	
1. Those whose medication compliance is < 70%	
2. Those who become pregnant during the study period	
3. Those who need surgery or inpatient treatment due to emergencies such as accidents or other illnesses	
4. Subject’s withdrawal of consent	
5. Subjects who have received prohibited medicines or therapies (e.g., anticoagulants, psychotropic drugs, and other drugs that may affect the symptoms of CHHF)	
6. Those who need standard treatment due to deterioration of symptoms of CHHF	
7. Occurrence of a serious adverse event	
8. Occurrence of factors making it difficult to sustain the process or investigator’s decision to terminate because of clinical trial results affected by some factors	

*CHHF* cold hypersensitivity in the hands and feet

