#### Safety outcome measure

The safety assessment will be performed for all subjects who have been randomized and received study medication more than once. The subjects’ vital signs and general physical status will be examined at every visit. Hematological examination (WBC, RBC, hemoglobin, platelet) and blood chemistry tests (blood urea nitrogen, creatinine, AST, ALT, gamma-glutamyl transpeptidase (γ-GTP)) will be performed at visits 1 and 4. Blood sugar test, thyroid function test (free T4, TSH), urine test, and pregnancy test (urine human chorionic gonadotropin) will be conducted at visit 1. The occurrence of adverse events (AEs) will be checked at visits 3, 4, and 5.

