### Statistical analysis

#### Efficacy assessment

For the efficacy assessment of this trial, both intention-to-treat (ITT) and per-protocol (PP) analyses will be performed. Missing data will be adjusted using the last-observation-carried-forward (LOCF) imputation method on ITT analysis. For the safety assessment of this trial, PP analysis will be conducted. The continuous variables will be expressed as the mean ± SD and the nominal variables will be reported as percentages. The ITT method will include all randomly assigned subjects, regardless of any protocol violations or study dropouts. The PP method will include only the subjects who have completed the 12-week study period without any major protocol violations and who have a compliance rate of ≥ 70%. The baseline characteristics will be compared by either a chi-square test for nominal variables or analysis of variance (ANOVA) for continuous variables. For the within-group analysis, the primary and secondary outcome variables will be assessed using a paired *t* test. The between-groups analysis after 8 weeks of administration will be performed using a repeated-measure ANOVA for the primary outcome variables, and a paired *t* test for the mean difference in the VAS score between the SDT group and the placebo group. As a secondary outcome variable, the mean differences in BT and WHOQOL-BREF scores between the groups will be analyzed using a repeated-measure ANOVA for BT and an ANOVA and post-hoc analysis for the WHOQOL-BREF scores. For all non-normal distribution data, a nonparametric statistical test will be performed. SPSS for windows version 23.0 (SPSS Inc., Chicago, IL, USA) will be used for statistical analysis. The statistical significance level will be set at *P* < 0.05.

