#### Safety assessment

Safety analysis will be conducted on all subjects who will be randomized and visited at least once after screening. Safety-related measures will be analyzed using the ITT method. The safety data will be stratified according to the symptoms.

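### Safety is assigned to the per-protocol set in one section and to two other populations elsewhere; the per-protocol version drops everyone withdrawn for a serious adverse event

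*Protocol article*

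**What the plan says.** The protocol article describes the safety population in three places.

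- **Statistical analysis, Efficacy assessment:** "For the safety assessment of this trial, PP analysis will be conducted". The same paragraph defines the set: "The PP method will include only the subjects who have completed the 12-week study period without any major protocol violations", with a further requirement of at least 70% compliance. It defines the alternative as follows: "The ITT method will include all randomly assigned subjects, regardless of any protocol violations or study dropouts".
- **Statistical analysis, Safety assessment:** "Safety analysis will be conducted on all subjects who will be randomized and visited at least once after screening", followed by "Safety-related measures will be analyzed using the ITT method".
- **Outcome, Safety outcome measure:** safety is assessed in "all subjects who have been randomized and received study medication more than once".

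The section on participant withdrawal also bears on the point. Anyone meeting a Table 3 criterion is discontinued from the trial, and item 7 of that table is "Occurrence of a serious adverse event". The section adds that women withdrawn after randomisation are still followed for outcomes and that their data are analysed by intention to treat.

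**The concern.** These are three explicit and incompatible statements. Shortening a protocol into an article can lose detail, but it does not produce three different populations for one analysis.

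The PP version does the most damage because membership depends on the outcome being measured. A woman withdrawn for an SAE is not a completer, so she is not in the set. Women who stop because they tolerate the product poorly can also leave, through low compliance (Table 3 item 1) or withdrawn consent (item 4).

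The other two versions have smaller faults. Read literally, the exposure condition in Safety outcome measure omits a woman who reacts to her first dose and takes no more. The ITT version puts women who never took the product in the denominator.

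Safety is in the trial's title and general aim, and the results are meant to inform a full trial. While the definitions conflict, the population could also be chosen after the results are known.

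**Working it through.** **No planned safety figure to reproduce.** The article gives no expected adverse event or SAE rate. The check compares the set definitions, then illustrates the size.

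**Step 1: the three populations side by side**

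| Section | Exposure needed | Completion needed | SAE withdrawal kept? | Single-dose stopper kept? | Never-dosed woman kept? |
|---|---|---|---|---|---|
| Efficacy assessment (PP) | compliance of at least 70% | 12 weeks, no major violation | no | no | no |
| Safety outcome measure | medicated more than once | none | yes, if dosed more than once | no, read literally | no |
| Safety assessment (ITT) | none | none | yes | yes | yes |

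Table 4 puts screening at visit 1 and randomisation at visit 2. Every woman randomised on schedule has therefore attended after screening, so the third row is in effect all randomised women and agrees with its own ITT wording. The count is three populations, not four.

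**Step 2: why PP loses every SAE withdrawal**

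1. An SAE meets Table 3 item 7.
2. Meeting a Table 3 criterion means discontinuation from the trial.
3. A discontinued participant has not completed the 12-week period.
4. PP contains only completers, so she is excluded.

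An SAE that did not lead to withdrawal before completion, for example one first recorded at the last visit, could stay in PP. The conclusion is limited to those withdrawn.

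**Step 3: size of the set**

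Inputs: 60 randomised, 30 per arm (Abstract; Randomization); 13% dropout (Sample size calculation). The 13% is the sample-size allowance. With difference 11.85, SD 15.255, two-sided 0.05 and an assumed power of 80% (not stated in the article), 2 × (15.255 × (1.960 + 0.842) / 11.85)² = 26.02 per arm, and 26.02 / 0.87 = 29.90, which rounds to the stated 30. Rounding up to 27 first would give 32.

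If dropout alone determined who is outside PP:

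- lost: 0.13 × 60 = 7.8, about 8 women
- remaining: 60 − 7.8 = 52.2, about 52 women

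Low compliance or major violations without dropout would add to the loss. For an assumed 5% to 30% outside PP, the loss is 0.05 × 60 = 3 to 0.30 × 60 = 18.

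**Step 4: effect on the reported SAE rate**

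Let k be the number withdrawn for an SAE (assumed values).

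| k | All randomised, k/60 | Counted in PP (about 52 women) |
|---|---|---|
| 1 | 1.7% | 0 |
| 2 | 3.3% | 0 |
| 3 | 5.0% | 0 |

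The PP column stays at zero whatever k is.

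**The case against.** The strongest reply is that the PP sentence is a slip. It stands under the efficacy heading, and neither section devoted to safety uses PP. The withdrawal section says withdrawn women are followed up and analysed by ITT. All adverse events must be recorded whether or not related to the product, and SAEs go to the review board and regulators within 24 hours. On this reading, nobody harmed would go unseen.

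Much of this is fair. It makes a drafting error likely, and it means the data would exist. But follow-up after withdrawal does not turn a discontinued woman into a completer, and expedited reporting protects oversight, not the comparative safety table. The sentence remains in the current text as an instruction to the analyst.

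Other objections limit the claim, and I accept them:

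- Only SAEs are named in Table 3. Women with non-serious events who complete with adequate compliance stay in PP, so it would be wrong to say that everyone harmed is excluded.
- PP drops women from both arms. Absolute rates are understated, but the direction of any between-arm bias depends on differential withdrawal, which the article does not give.
- The 13% is a dropout allowance and not a rate of withdrawal for harm. The figure of 8 shows how far the set may shrink, not how many events are lost.
- Medication is dispensed at the randomisation visit, so the exposed set and the ITT set probably differ by few women. The material conflict is PP against the other two.

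**Conclusion.** The concern holds. The article assigns safety to three populations that cannot be reconciled by reading, and the PP version excludes by definition every participant withdrawn for an SAE. This part needs no numerical assumption; it follows from Table 3 and the PP completion rule.

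The illustrative figures rest on assumed SAE counts and on equating the 13% dropout with PP exclusion. They show the scale and do not predict it. No claim is made that SDT would be favoured over placebo. No sample size or power figure changes.

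**What to change.** Define one safety set and state it identically in Safety outcome measure, Efficacy assessment and Safety assessment: all randomised participants who took at least one dose of study medication, analysed by the treatment actually received. Specifically:

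1. Delete the sentence in Efficacy assessment that assigns safety to PP.
2. In Safety outcome measure, change the exposure condition from more than one dose to at least one dose.
3. In Safety assessment, replace the visit-based definition and the ITT sentence with the same set.

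Analysis by treatment received is the usual convention; the article reports no dispensing errors, so it may change nothing in practice.

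The cost is wording only. Data collection and trial conduct are unaffected. When the article was written recruitment was still open, with 50 participants enrolled, and the database is to be locked only after the trial is completed. The definition can therefore be fixed before the lock and before unblinding, so that it is not chosen with results in view.

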### Randomization

Suitable participants, who agree to participate in this RCT, will be randomly assigned to a treatment group (SDT) or a placebo group at a 1:1 ratio. Thirty subjects will each be allocated to the SDT and placebo groups. A web-based randomization system (WBRS) developed by the contract research organization (CRO), the Institute of Safety and Effectiveness Evaluation for Korean Medicine (ISEE), will perform the assignment. The random order will be generated by the CRO’s independent professional statistician using the SAS 6.1 program and stratified by the hospital using random block sizes of two and four based on the allocation code provided by the SAS system.

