### Outcome

#### Primary outcome measure

The change in the VAS score between visit 2 (baseline) and visit 4 (after treatment) will be used as the primary outcome measure. The mean difference between the change scores of the two groups will be calculated.

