#### Sample size calculation

The change in the VAS score between visit 2 (baseline) and visit 4 (after treatment) will be used as the primary outcome measure. The hypotheses are as follows:H0: δ = Δ1 – Δ2 = 0H1: δ = Δ1 – Δ2 ≠ 0

where Δ1 is the average change in the VAS score between visit 4 and visit 2 in the SDT group, and Δ2 is the average change in the VAS score between visit 4 and visit 2 in the placebo group

Based on a similar study [17], the expected average VAS score difference in the SDT group is 11.85 (larger than 10, because in the study used as a reference a 100-mm VAS was applied to assess severity of CHHF, and the scores ranged from 0 to 100), and the standard deviation (SD) is estimated to be 15.255 using the pooled standard deviation formula. Considering a dropout rate of 13%, which is agreed among medical experts, we need to recruit 30 subjects per arm to calculate the treatment efficacy, and to offer the power calculation for a future large-scale RCT.

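### The primary between-group test is not tied to the visit 2 to visit 4 VAS contrast: an unspecified repeated-measures ANOVA stands beside an invalid paired t test, with no baseline or hospital covariate

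*Protocol article*

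**What the plan says.** The Primary outcome measure section fixes a single contrast: "The change in the VAS score between visit 2 (baseline) and visit 4 (after treatment) will be used as the primary outcome measure", followed by "The mean difference between the change scores of the two groups will be calculated". The Sample size calculation section sets a two-sided hypothesis on the same quantity, the SDT mean change minus the placebo mean change.

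The Efficacy assessment section then names two between-group procedures for VAS in one sentence. The first is "The between-groups analysis after 8 weeks of administration will be performed using a repeated-measure ANOVA for the primary outcome variables". The second is a paired t test, applied to the mean VAS difference between the SDT and placebo arms. The section sets the level ("The statistical significance level will be set at *P* < 0.05") but does not say which of the two results is primary.

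VAS is recorded at all five visits (Visual Analogue Scale section and Table 4). Under Randomization, allocation is "stratified by the hospital using random block sizes of two and four", with five hospitals taking part. The analysis text names no covariate.

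**The concern.** A repeated-measures ANOVA is a family of tests. With VAS at five visits, the result depends on which visits enter and on whether the group effect or the group-by-time interaction is read. Only one of those choices is the contrast that the outcome section defines.

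The second test does not close the gap. A paired t test needs pairs, and participants in parallel arms have none. Its result would depend on an arbitrary matching of rows, and it cannot use everyone if the arms end up unequal.

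Two undesignated tests, one of them with its tested term open, leave room to choose after the data are seen. The trial is also meant to supply the power calculation for a later RCT, so the week 8 difference and its interval are its main product. A VAS baseline is scheduled at visit 2 and hospital is known for everyone, yet neither is used as a covariate to sharpen that interval.

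**Working it through.** **Inputs from the Sample size calculation section.** The effect: "the expected average VAS score difference in the SDT group is 11.85", on a 0 to 100 mm scale. The spread: "the standard deviation (SD) is estimated to be 15.255 using the pooled standard deviation formula". Allowing for 13% loss, the plan recruits 30 per arm. Two-sided alpha is 0.05.

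**Assumptions.** 11.85 is the between-arm difference and 15.255 is the SD of the change. Power is not stated, so 80% is tried. The correlation rho between visit 2 and visit 4 VAS is not given, so a range is used.

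**1. The plan's own figure.** n per arm = 2(1.960 + 0.842)² × 15.255² / 11.85² = 26.02. Taking 26, 26/(1 − 0.13) = 29.9, so 30. The stated size therefore matches an unadjusted two-sample comparison of mean change at 80% power by the normal approximation. This supports reading the two inputs as above.

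**2. The unadjusted change test.** At 26 per arm, SE = 15.255 × √(2/26) = 4.231 and the noncentrality is 11.85/4.231 = 2.80. With 50 df the critical value is 2.009. Power is 78.4% and the half-width is 2.009 × 4.231 = 8.5 mm. At 30 per arm, the ITT count with LOCF, SE = 3.939. Power is then 84% and the half-width 7.9 mm.

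**3. Which repeated-measures test equals the change test.** Simulation used 26 per arm, compound symmetry, rho 0.3, 0.5 and 0.7, and 6,000 runs per setting.

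| Visits and term | Power |
|---|---|
| Visits 2 and 4, group by time | about 78%; p values equal those of the change t test |
| Visits 2 to 4, group by time, half the effect at week 4 | about 70% |
| Visits 2 to 4, group by time, full effect at week 4 | about 82–83% |
| Visits 2 to 5, group by time | about 63–83%, by effect profile |
| Visits 2 and 4, group main effect | about 52 / 35 / 21% at rho 0.3 / 0.5 / 0.7 |

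Only the first row estimates the stated contrast. The three-visit and four-visit interactions are multi-df tests, which can gain or lose power but give no week 8 difference. The main effect averages in a pre-treatment visit.

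**4. ANCOVA on visit 2 VAS.** With equal variances at the two visits, residual SD = 15.255 × √((1 + rho)/2). At 26 per arm:

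| rho | residual SD | power | half-width |
|---|---|---|---|
| 0.3 | 12.30 | 92.6% | 6.9 mm |
| 0.5 | 13.21 | 88.7% | 7.4 mm |
| 0.7 | 14.06 | 84.6% | 7.8 mm |
| 0.8 | 14.47 | 82.5% | 8.1 mm |

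**5. Unequal variances.** Let k = baseline SD / week 8 SD. The variance ratio of ANCOVA to change is (1 − rho²)/(1 + k² − 2·rho·k). For an assumed k = 0.7 it is 0.850, 0.949 and 1.000 at rho 0.3, 0.5 and 0.7, giving power of 84.5%, 80.4% and 78.4%. When rho = k the regression slope is 1, so ANCOVA and the change analysis coincide and the gain vanishes.

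**6. Hospital.** No between-site variance is given. If site explained 2%, 5% or 10% of the variance of change (assumed), adding hospital to the change analysis would move power from 78.4% to 79.1%, 80.3% or 82.4%.

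**7. Cost in degrees of freedom.** Baseline takes 1 and five hospitals take 4, so 50 df become 45. At rho 0.3 power falls from 92.60% to 92.49%, and at rho 0.8 from 82.51% to 82.35%: at most about 0.2 points.

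**The case against.** The strongest reply is that the protocol does point to week 8. The outcome and hypothesis are stated clearly, the analysis sentence places the comparison at the end of 8 weeks, and a two-visit interaction is exactly the change test. This stands. A reader might infer that the planned ANOVA misses the week 8 change, or that it necessarily costs power. The documents support neither. The low main-effect powers in the table come from a reading that the stated hypothesis does not call for, and an interaction test over more visits beats the change test when the effect is early and sustained. The documents leave the test open; they do not choose the wrong one.

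It is also too strong to say that baseline is ignored, since it enters through the change score or as a repeated level. What is absent is its use as a covariate.

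The size of the ANCOVA gain can fairly be challenged. It rests on an assumed correlation and equal variances, and the screening requirement of VAS ≥ 4 cm may narrow baseline spread. The 26 per arm is an evaluable count, whereas ITT with LOCF keeps 30.

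Finally, covariates and model terms are often left to an analysis plan that is not shown. That would excuse silence. It does not excuse naming two procedures for one primary contrast, one of them unsuited to the design. The paired test may be a slip, because the same section properly uses a paired t test within groups, but as written it is wrong. A post-hoc step for WHOQOL-BREF could refer to visits rather than groups, so it is not counted as an error here.

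**Conclusion.** The point holds in limited form. The primary between-group test is not tied to the contrast that the protocol defines: the visits and tested term of the repeated-measures ANOVA are open, the accompanying paired t test is invalid for independent arms, and no test is named as decisive. These defects follow from the text and need no assumption.

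The absence of baseline and hospital covariates is a missed improvement, not an error that biases the result. On the assumptions above, baseline adjustment at 26 per arm lifts power from 78% to between 82% and 93% and cuts the half-width from 8.5 mm to between 8.1 and 6.9 mm. Under a narrow baseline spread the gain may be about zero. The gain from hospital is unknown.

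This should be corrected, with high confidence in the mis-specification and only moderate confidence in the size of the gain.

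**What to change.** - Name one primary analysis: ANCOVA of visit 4 VAS on treatment, visit 2 VAS and hospital, reporting the adjusted difference and 95% CI. An equivalent choice is the visit 4 contrast of a mixed model with those covariates plus visit and treatment-by-visit.
- Delete the between-arm paired t test. The within-group paired tests may stay as description.
- Make the repeated-measures ANOVA supportive, stating its visits and the term tested.
- Use the same baseline- and hospital-adjusted model for BT and WHOQOL-BREF, and say what any post-hoc comparison compares.

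These are wording changes, best made before the database is locked. No data collection changes, since VAS and BT at visits 2 and 4, WHOQOL-BREF at those visits and hospital are all already recorded. The statistical cost is about five degrees of freedom, at most about 0.2 points of power.

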### Study design and setting

This is a 12-week pilot, randomized, double-blind, two-arm, placebo-controlled, parallel-group, multicenter clinical trial that will be conducted in Gachon University Gil Korean Medical Hospital, Korean Medical Hospital of Sangji University, Semyung University Second Affiliated Korean Medical Hospital at Chungju, Kyung Hee University Korean Medical Center, and Kyung Hee University Korean Medicine Hospital at Gangdong in Korea.

A written informed consent will be obtained from each subject by the principal investigator (PI) or researcher after the subject has received sufficient explanation and a period of time in which to make a thoughtful decision. Each subject will be screened up to 7 days prior to randomization. Once they receive the trial subject identifier, they will be treated for 8 weeks and asked to visit the site every 4 weeks for safety and efficacy assessments. A follow-up visit will occur at 4 weeks after the end of the administration. The participants will be asked to return any unused investigational drugs at visit 3 and visit 4 in order to calculate drug compliance. During the trial, the participants will be prohibited from receiving other medications related to CHHF. The protocol design is based on the Consolidated Standards of Reporting Trials (CONSORT) guidelines and Standard Protocol Items: Recommendations for Interventional Trials (SPIRIT) checklist (see Additional file 1). Figure 1 presents a schematic flow diagram of the study.

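### The between-group comparison of VAS change is assigned a paired t test although the two arms are independent, so its P value depends on an undefined pairing of patients

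*Protocol article*

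**What the plan says.** The design is described as a "pilot, randomized, double-blind, two-arm, placebo-controlled, parallel-group, multicenter clinical trial" (Study design and setting). Women "will be randomly assigned to a treatment group (SDT) or a placebo group at a 1:1 ratio", and the list is "stratified by the hospital using random block sizes of two and four" (Randomization). Neither section describes a crossover or matched pairs.

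The primary outcome is the change in VAS from visit 2 to visit 4. Of this change the article says: "The mean difference between the change scores of the two groups will be calculated" (Primary outcome measure). The Sample size calculation section states the two-sided null hypothesis δ = Δ1 − Δ2 = 0, where Δ1 and Δ2 are the mean changes in the SDT and placebo groups.

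The Efficacy assessment section then names three analyses of the primary outcome:
- Within groups: "For the within-group analysis, the primary and secondary outcome variables will be assessed using a paired *t* test".
- Between groups: "a repeated-measure ANOVA for the primary outcome variables".
- Between groups, in the same sentence as the ANOVA: "a paired *t* test for the mean difference in the VAS score between the SDT group and the placebo group".

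**The concern.** A paired t test analyses differences within pairs that the design has linked, such as two measurements on one woman or two matched women. Here each woman belongs to one arm and has no counterpart in the other. Stratifying by hospital in blocks of two and four balances numbers but does not define partners.

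The wording cannot be read as the within-patient change from baseline. That test is assigned separately in the preceding sentence, and the clause in question names both arms.

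An analyst who follows the text has two options, and neither is sound. One is to pair patients by something arbitrary such as row order, so that the same data can give different P values. The other is to run a paired test inside each arm and contrast the two P values, which does not test δ = 0. The clause is the one attached to the between-group mean difference that the article defines as its primary outcome, so the choice bears directly on the primary objective.

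**Working it through.** **Inputs.** From the Sample size calculation section: difference 11.85 and SD 15.255, both on a 0 to 100 mm scale; dropout 13%; 30 per arm. Two-sided alpha of 0.05 follows from the stated hypothesis and the Efficacy assessment section. Assumptions: 80% power (none is stated), 11.85 taken as the between-arm difference, and 15.255 as the SD of the change in each arm.

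**1. Which test does the stated sample size fit?**
- Two independent means: n = 2 × [15.255 × (1.960 + 0.842) / 11.85]² ≈ 26.0 per arm. Then 26 / 0.87 = 29.9, so 30, as stated. Strict rounding up to 27 gives 27 / 0.87 = 31.03, so 32.
- Single-sample or paired variance: n = [15.255 × 2.802 / 11.85]² ≈ 13.01, so 14. Then 14 / 0.87 = 16.1, so 17.

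The stated 30 matches the independent comparison and not the paired one.

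**2. How far does the P value move with the pairing?** Take 26 per arm and an observed difference that gives a two-sample P of exactly 0.050. The standard error is 15.255 × √(2/26) = 4.231 and the critical t on 50 df is 2.009, so the difference is 8.50 mm.
- With equal SDs, the paired statistic is t = 8.50 / [4.231 × √(1 − r)] on 25 df, where r is the correlation that the chosen pairing happens to produce.
- Over random pairings r has mean 0 and SD 1/√25 = 0.2, so about 95% of pairings fall between −0.4 and +0.4.
- At r = −0.4, t = 1.70 and P = 0.102. At r = 0, t = 2.01 and P = 0.056. At r = +0.4, t = 2.59 and P = 0.016.
- Simulation agrees: 20,000 random pairings of one such data set gave about 0.018 to 0.102 (central 95%), with 42% below 0.05.
- In another data set (difference 8.6, two-sample P = 0.047), pairing the values after sorting both arms in the same direction gave P of about 10⁻¹⁴.

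**3. Error rate and power if pairing ignores the outcome.** From 100,000 simulated trials per scenario for type I error, and the noncentral t distribution for power:

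| Per arm | Type I error, paired | Power, independent t | Power, arbitrary pairs |
|---|---|---|---|
| 26 | 5.1% | 78.4% (df 50) | 76.8% (df 25) |
| 30 | 5.0% | 84.1% (df 58) | 82.8% (df 29) |

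**4. Unequal arms.** If each of 30 women per arm completes with probability 0.87, the chance that the completer counts differ is 1 − Σ P(k)², with P(k) binomial (30, 0.87). This is 0.846, or about 85%.

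**5. If two within-arm tests are contrasted instead.** Suppose both arms truly change by the same amount and p is the chance that one arm's paired test is significant. Then SDT is significant and placebo is not with probability p(1 − p). With 26 per arm and SD 15.255:

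| Common change (assumed, mm) | p | p(1 − p) |
|---|---|---|
| 0 | 0.050 | 4.8% |
| 2 | 0.099 | 8.9% |
| 4 | 0.251 | 18.8% |
| 6.1 | 0.500 | 25.0% |
| 10 | 0.895 | 9.4% |
| 11.85 | 0.968 | 3.1% |

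The documents give no expected common change, so the result is a range of about 3% to 25%. The upper end is the mathematical maximum of p(1 − p).

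**The case against.** The strongest reply is that the plan already contains a legitimate between-group analysis. The same sentence names a repeated-measures ANOVA. If only visits 2 and 4 enter, its group-by-time term is equivalent to a two-sample t test on the change. A reader might infer that the paired test produces the trial's headline P value, but the article does not rank the two, so that cannot be claimed. What remains is that two unranked tests are named and one of them has no pairs to work on.

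A reader might also infer an inflated false-positive rate. The figures do not support that: pairing made blind to outcome keeps the rate near 5% and costs under 2 points of power. The harm is a result that is not unique. The spread of 0.018 to 0.102 is moreover computed at the significance threshold, where a shift in P matters most, and so it does not describe typical data.

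It would likewise be too strong to say that the test cannot be run. The ITT set includes everyone randomized, with LOCF for missing values, so if 30 per arm is reached the ITT arms are equal and software would produce an answer. The obstacle lies mainly in the per-protocol set.

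Finally, the article nowhere says that two within-arm P values will be contrasted, and its definition of the primary outcome points away from that reading. Since the sample size fits independent groups and this is a pilot, the word may be a slip. That bears on how the error arose; the sentence still needs correcting.

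**Conclusion.** The point holds as an inapplicable test written into the between-group analysis of the primary outcome. It contradicts the article's own design, hypothesis and sample size basis. This is not a detail left to an analysis plan, because the article names a test and names the wrong one.

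Its size is as follows. The P value is not unique, with a central 95% spread of about 0.018 to 0.102 around a two-sample P of 0.050 at 26 per arm. The chance that per-protocol arms differ in number, so that patients would have to be dropped, is about 85%; this assumes independent 13% dropout from 30 per arm and takes completers as a stand-in for the per-protocol set. If within-arm tests were contrasted instead, a false contrast in favour of SDT would arise in about 3% to 25% of trials for an assumed common change of 0 to 11.85 mm. The documents do not support general inflation of type I error, or the claim that this test alone decides the trial. The lack of a stated deciding test is part of the defect.

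**What to change.** In the Efficacy assessment section, replace the between-group paired t test with an independent-groups comparison of the visit 2 to visit 4 VAS change: a two-sample t test, or ANCOVA with baseline VAS as covariate. Choose one of these in advance and report the mean difference with its 95% CI. Name it as the single primary analysis and the repeated-measures ANOVA as supportive. Keep the paired t tests as descriptive within-arm summaries that carry no efficacy conclusion.

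The cost is a sentence or two of text. The 30 per arm stands, because it already fits two independent means, and no data collection changes. The article reports recruitment as still open and places analysis after database lock, so the correction can be made before any outcome is analysed.
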